### Sample Size

Sample size projections were based on a power analysis using SAS Proc GLMPower. In the latest pilot study by WHCCS, group differences in pain of 8 percentage points after 3 months of treatment were observed[42]. Informed by these results, the scientific literature,[31,101] and consensus of study investigators and clinicians, we are interested in detecting an 8 percentage point difference between the two group means in patient-rated leg pain at the short- and long-term. In our pilot study, correlation coefficients among the pain variable over time varied from r = 0.22-0.25 and estimates of standard deviation were 1.7 (scale 0-10).

Using these estimates, the sample size calculation based on the analysis of covariance at one time point, adjusting for the baseline value, indicates 80 patients per group are required to achieve 86% power at the 0.05 level of significance to detect a difference between groups of 8 percentage points.

The same data analysis approach will be used to analyze the secondary outcome variables as confirmatory analyses to assist with the interpretation of study results. A more conservative Bonferroni-adjusted level of significance will be used to judge the results as statistically significant.

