### Patient Satisfaction

Patient satisfaction is measured on 7-point scale (1 = poor, 7 = excellent) using eight questions addressing different aspects of patient care[53].

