### Improvement

Patient-rated improvement is an important, patient-oriented outcome measure that has been demonstrated to be reliable and responsive[77-79]. Patients are asked to use the 9-point scale to compare their BRLP condition to what it was before study treatment. Response choices are No symptoms (100% improvement), Much better (75% improvement), Somewhat better (50% improvement), A little better (25% improvement), No change (0% improvement), A little worse (25% worse), Somewhat worse (50% worse), Much worse (75% worse), and Twice as bad (100% worse).

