### Data Analysis

Effects in patient-rated leg pain between groups will be assessed by modeling over weeks 3, 12, 26, and 52 adjusting for the baseline value of leg pain and the baseline variables used in the minimization algorithm for treatment allocation. Mixed models, using SAS Proc Mixed, will be used to examine patterns and estimate effects between groups after fitting models that account for the correlation across measurements in the same patient and using the variance-covariance structure that best fits the data[99,100]. Normality assumptions will be evaluated through normal probability plots and transformations explored if necessary. We will test for site-by-group and time-by-group interactions. A level of significance of 0.05 will be used to judge the results as statistically significant. Adjusted mean differences and 95% confidence intervals between groups at weeks 3, 12, 26, and 52 will be presented in tables and line graphs. Further adjustment will control for unbalanced baseline and other possible confounding variables to increase precision of the estimates. An intention-to-treat analysis will be used; all patients with at least one follow-up measure will be included in the analysis, as the methods do not require data at every time point.

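### Secondary outcomes are judged at a plain Bonferroni level; Holm's procedure gives the same familywise error control and is never less powerful

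*Protocol article*

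**What the plan says.** The rule for the secondary outcomes stands at the end of the Sample Size section of the protocol article. On the model: "The same data analysis approach will be used to analyze the secondary outcome variables as confirmatory analyses to assist with the interpretation of study results". On the threshold: "A more conservative Bonferroni-adjusted level of significance will be used to judge the results as statistically significant". The article does not say how many tests share the adjusted level.

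The approach referred to is the one in Data Analysis: a mixed model of the four follow-up assessments, from week 3 to week 52. Its adjustment is described as follows: "adjusting for the baseline value of leg pain and the baseline variables used in the minimization algorithm for treatment allocation". The threshold for leg pain is given separately: "A level of significance of 0.05 will be used to judge the results as statistically significant". Adjusted mean differences are to be reported with ordinary 95% confidence intervals.

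Eleven self-report secondary measures follow the primary outcome: low back pain, bothersomeness, frequency, disability, SF-36, fear avoidance, satisfaction, improvement, medication use, EuroQol and self-efficacy. Two of them describe the period after treatment starts. For improvement: "Patients are asked to use the 9-point scale to compare their BRLP condition to what it was before study treatment". Satisfaction is rated "using eight questions addressing different aspects of patient care".

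**The concern.** The secondary analyses are called confirmatory and are meant to help interpret the leg pain result. Many of them (back pain, bothersomeness, frequency, disability, quality of life) are related measures of one condition, so if manipulation works, several may move together. That is the setting in which plain Bonferroni gives up power that a step-down procedure keeps. The article names Bonferroni, so the choice has been made and not left open.

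The second, smaller matter is the model. Carried over to a secondary outcome, the leg pain model would adjust for that outcome's own baseline value. Improvement is itself a comparison with the state before treatment, so it has no such value. The same is inferred for satisfaction, which rates care received. The Data Collection section lists baseline among the times for self-report measures without excepting these two. The Patient Expectation of Care section describes a pre-treatment rating on the improvement scale, but that rating measures expectation and is not a baseline value of improvement.

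**Working it through.** **Inputs.** From Sample Size: 80 per group, difference 8 percentage points (0.8 on the 0-10 scale), SD 1.7, correlation 0.22-0.25, level 0.05, stated power 86%. Two-sided testing is assumed, since 95% intervals are planned. The number of secondary tests m is not given, so a range is used:
- m = 11, one score for each listed measure;
- m = 20, with eight SF-36 domains, two fear-avoidance subscales and two medication items counted separately: 1+1+1+1+8+2+1+1+2+1+1 = 20.

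**Step 1: reproduce the stated power.** The residual SD is 1.7 × √(1 − r²), which is 1.658 at r = 0.22 and 1.646 at r = 0.25. The noncentrality is 0.8 / (residual SD × √(2/80)), which is 3.05 and 3.07. Normal-approximation power is Φ(3.05 − 1.96) = 86.2% and Φ(3.07 − 1.96) = 86.7%. With the noncentral t on 157 df it is 85.8% and 86.3%. The plan's 86% is reproduced.

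**Step 2: Bonferroni power for a secondary outcome with the same standardized effect (r = 0.25).**
- m = 11: level 0.05/11 = 0.0045, critical value 2.838, power Φ(3.074 − 2.838) = 59%.
- m = 20: level 0.05/20 = 0.0025, critical value 3.023, power Φ(3.074 − 3.023) = 52%.

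**Step 3: Holm.** Order the p-values. Compare the smallest with 0.05/m, the next with 0.05/(m − 1), and so on, stopping at the first failure. No threshold is below 0.05/m, so every Bonferroni rejection is also a Holm rejection. Each method makes at least one rejection exactly when the smallest p-value is at most 0.05/m, so the chance of any rejection is identical.

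**Step 4: size of the gain.** Simulation of at least 100,000 replicates of m normal test statistics, noncentrality 3.074 for each true effect, pairwise correlation 0 to 0.5. The table gives average power per truly affected outcome.

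| m | True effects | Bonferroni | Holm |
|---|---|---|---|
| 11 | 1 | 59-60% | 59-60% |
| 11 | 2 | 59% | 60% |
| 11 | 5 | 59% | 62-63% |
| 11 | 8 | 59% | 65-66% |
| 11 | 11 | 59% | 71-73% |
| 20 | 1 | 52% | 52% |
| 20 | 10 | 52% | 56% |
| 20 | 20 | 52% | 64% |

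The simulated chance of at least one rejection was equal under the two methods in every row. Where some outcomes were unaffected, the chance of a false rejection stayed below 0.05 under both (for example 0.027 and 0.038 with m = 11, five true effects and correlation 0).

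**Step 5: the model for improvement and satisfaction.** The leg pain model contains treatment, time, the minimization variables and a baseline value. For these two outcomes every term except the own-baseline term is available, and baseline leg pain is measured in all patients.

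**The case against.** Bonferroni is not a mistake. It controls the familywise error rate, the article openly calls it conservative, and the trial is powered on leg pain only. All of that stands, and it makes the change an improvement and not a correction. Bonferroni also comes with simple simultaneous confidence intervals, which Holm lacks. That is true but weighs little here, because the plan reports ordinary 95% intervals and not simultaneous ones.

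The gain is small unless many outcomes respond: 0-1 point with one or two true effects and about 3 points with five of eleven. That also stands.

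A reader might infer three stronger things that the document does not support.
- **The secondary outcomes have little chance of helping.** Bonferroni power is 59% to 52% with 80 per group. With 96 per group (the planned 192 patients split equally, an assumption) it is 70% to 64%.
- **The rule spans about 80 tests,** that is 20 scores at four weeks. The article gives no family size and describes one mixed model over the four weeks. Leaving the family to a fuller document is ordinary for an article.
- **The stated model cannot be run for improvement and satisfaction.** The article promises the same approach, not an identical covariate list. Only one term is unavailable, and an analyst would drop or replace it. For satisfaction even that rests on inference.

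**Conclusion.** The point holds as an optional, low-cost improvement. At the same familywise error rate Holm is never less powerful than the planned Bonferroni rule. With 11 measures it adds nothing with one true effect, about 3 points with five, 6-7 with eight and 12-14 with all eleven. With 20 scores it adds about 4 points with ten true effects and 12 with all twenty.

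These figures assume that each affected outcome carries the full standardized effect of leg pain, with two-sided tests, 80 per group and correlation 0 to 0.5 between test statistics. The document supports the effect size for leg pain only, so the larger gains are a best case. The missing own-baseline term for improvement, and by inference for satisfaction, is a minor clarification.

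**What to change.** In Sample Size, replace the Bonferroni-adjusted level with Holm's step-down procedure at familywise level 0.05, applied to whatever family of secondary outcomes the trial already intends. Keep the adjusted differences with 95% confidence intervals as planned. Add one sentence: for patient-rated improvement and satisfaction, the model uses baseline leg pain and the minimization variables in place of an own-baseline value, and the pre-treatment expectation rating is not used as that value.

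The cost is wording only, with no new data, no added patients and no change to the primary analysis. The one statistical cost is that Holm decisions have no simple matching simultaneous intervals, so an ordinary 95% interval can exclude zero for an outcome that Holm does not reject. The same already happens under Bonferroni with the planned 95% intervals. Restricting tests to one week, testing the secondary outcomes only after a significant primary result, or choosing one score per measure are separate design choices that this point does not require.

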### Missing Data

Every effort is made to prevent the occurrence of missing data. The mixed model analysis includes all patients that have at least one follow-up assessment. To examine the possible effects of missing data on the results, SAS Proc MI will be used to produce multiple imputation analyses. The Markov Chain Monte Carlo approach will used to impute all missing values of the outcome variables from baseline demographic characteristics and the baseline primary and secondary outcome measures. We will draw 5-15 imputations and fit the same mixed model analysis described above. SAS Proc MIAnalyze will be used to combine the results to obtain estimates of regression coefficients, standard errors and p-values[102,103].

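### The imputation model for the missing-data analysis omits treatment arm, so that sensitivity estimate is pulled towards zero by up to about the missing fraction

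*Protocol article*

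**What the plan says.** The Missing Data section gives the purpose of the analysis: "To examine the possible effects of missing data on the results, SAS Proc MI will be used to produce multiple imputation analyses". It then fixes the method, MCMC, and the predictors: the run will "impute all missing values of the outcome variables from baseline demographic characteristics and the baseline primary and secondary outcome measures". All of these predictors are measured at baseline. The next step is "We will draw 5-15 imputations and fit the same mixed model analysis described above", with the results combined in Proc MIAnalyze.

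The model referred to is in the Data Analysis section. It compares the groups over weeks 3, 12, 26 and 52, adjusts for baseline leg pain and the minimisation variables, and is meant to "account for the correlation across measurements in the same patient". It also carries interactions with group: "We will test for site-by-group and time-by-group interactions". Its analysis set is restricted: "all patients with at least one follow-up measure will be included in the analysis".

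Neither section mentions arm as an imputation predictor or imputation carried out within arm.

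**The concern.** An imputation model should contain at least what the later analysis model estimates. Here the later model estimates the group difference and the imputation model, as listed, does not know the group. Randomisation and minimisation make the listed baseline variables similar in the two arms, so they cannot stand in for it. Imputed values in both arms then come from nearly the same distribution, and each imputed patient dilutes the contrast.

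The interpretation of the sensitivity analysis is at stake. Its purpose is to show whether missing data affect the result. With arm left out, it is expected to differ from the primary analysis even when missingness is harmless. A reader who sees a smaller imputed estimate could not tell a real effect of missing data from a by-product of the imputation model.

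**Working it through.** **Inputs.** From Sample Size: a difference of 8 percentage points, that is 0.8 on the 0-10 scale; SD 1.7; correlation of pain over time 0.22-0.25. From Study Population: 192 patients, taken here as 96 per arm. From the two evaluation sections: earlier published follow-up of 90-97% at time points like weeks 3 and 12 (3-10% missing) and 85-100% at time points like weeks 26 and 52 (0-15% missing).

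**Check of the inputs against the plan's own figure.** The article states 86% power with 80 per group. With baseline adjustment the SD is 1.7 × √(1 − r²), and power = Φ(0.8 / (SD × √(2/80)) − 1.96).
- r = 0.22: SD 1.658, SE 0.262, ratio 3.051, power 86.2%
- r = 0.25: SD 1.646, SE 0.260, ratio 3.074, power 86.7%

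The noncentral t gives 85.8% and 86.3%. The stated figure reproduces with a two-sided test and is not in dispute; it confirms that the inputs are read correctly.

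**Reading A: baseline predictors only, as the words stand.** Let m be the missing fraction, equal in both arms. Observed patients contribute the full difference δ and imputed patients contribute none, so the estimate is δ × (1 − m).
- m = 3%: 0.8 × 0.97 = 0.776
- m = 10%: 0.8 × 0.90 = 0.72
- m = 15%: 0.8 × 0.85 = 0.68

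**Reading B: arm omitted, but observed pain at the other visits informs the imputation through the joint model.** Those scores carry part of the arm effect. The estimate is δ × (1 − m(1 − b)), where b is the sum of the regression coefficients on the other three visits.
- Given baseline, at correlation 0.235: variance 2.89 × (1 − 0.235²) = 2.730; covariance 2.89 × (0.235 − 0.235²) = 0.520.
- Ignoring arm adds δ²/4 = 0.16 to each: 2.890 and 0.680.
- b = 3 × 0.680 / (2.890 + 2 × 0.680) = 0.48.
- m = 10%: 0.8 × (1 − 0.10 × 0.52) = 0.758. m = 15%: 0.8 × (1 − 0.15 × 0.52) = 0.738.

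If the follow-up visits correlate at 0.6 (assumed), the covariance given baseline is 2.89 × (0.6 − 0.235²) = 1.574. Adding 0.16 gives 1.734, so b = 5.202 / 6.358 = 0.82. The estimates are then 0.786 and 0.778.

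**Simulation.** Settings: 192 patients, true difference 0.80 at every visit, baseline correlation 0.235, 10% missing at weeks 3 and 12 and 15% at weeks 26 and 52, completely at random and independently by visit, 5 imputations, 300 replicates. Chained normal regressions stand in for MCMC, and ANCOVA at each visit stands in for the mixed model. Monte Carlo SE is about 0.013-0.016.

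| Imputation model | Follow-up correlation | Wk 3 | Wk 12 | Wk 26 | Wk 52 |
|---|---|---|---|---|---|
| Baseline only, no arm | 0.235 | 0.735 | 0.715 | 0.695 | 0.689 |
| Other visits, no arm | 0.235 | 0.771 | 0.750 | 0.751 | 0.743 |
| Other visits and arm | 0.235 | 0.814 | 0.796 | 0.822 | 0.810 |
| Baseline only, no arm | 0.6 | 0.720 | 0.733 | 0.693 | 0.698 |
| Other visits, no arm | 0.6 | 0.783 | 0.806 | 0.793 | 0.795 |
| Other visits and arm | 0.6 | 0.800 | 0.819 | 0.819 | 0.822 |

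Within each correlation the models were applied to the same simulated data, so differences between rows are the cleaner comparison. At week 52 and correlation 0.235 the loss is 0.810 − 0.689 = 0.121 under A (formula: 0.15 × 0.8 = 0.12) and 0.810 − 0.743 = 0.067 under B (formula: 0.062). At correlation 0.6 the loss under B is 0.822 − 0.795 = 0.027 (formula: 0.022).

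**Effect on significance.** In separate simulations of week 52 alone (correlation 0.25, 15 imputations, 15% missing), baseline-only imputation gave 0.67 and was significant in 0.74-0.75 of trials, against 0.82-0.85 with arm included. Under reading B the figures were 0.73 and 0.82, against 0.85 with arm.

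**The case against.** Four points can be made for the plan.

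- **The joint model may use the follow-up scores.** MCMC in Proc MI fits one multivariate normal model to all variables in the run. A reader might infer from the predictor list that observed follow-up pain is ignored; the text does not settle that. This stands, and it is why the size is given under two readings. It does not remove the fault: arm is absent under both, and at the pilot correlation some shrinkage remains. For a patient with no follow-up at all, the joint run has only baseline to work with, so reading A applies.
- **The error is bounded and conservative.** It goes towards no difference, by no more than about the missing fraction, in a secondary analysis. This stands too. A reader might infer that the analysis cannot check the primary result at all, or that the primary result is compromised. Neither follows: the check is biased, and the primary mixed model contains group and uses all observed visits.
- **The statistical analysis plan, not shown, may include arm.** Possibly. But the article names the procedure, the method, the predictors and the pooling step. This is a stated list, and if another document differs, the list needs correcting.
- **Other criticisms are preferences.** The imputation assumes data missing at random, as the mixed model does, but the article claims no test of that assumption. No calculation shows 5-15 imputations to be too few at 15% missing or less. Neither is an error. Scenarios such as 25% missing lie outside the cited rates and are not relied on here.

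**Conclusion.** The point holds in limited form. The stated imputation predictors omit the variable whose effect the later model estimates, so the sensitivity estimate is biased towards zero even under the most benign missingness.

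At the cited follow-up rates the loss on the literal reading is 0-15% of the effect: 0.80 becomes 0.72-0.78 at weeks 3 and 12, and 0.68-0.80 at weeks 26 and 52 (about 0.67-0.68 at the 15% limit across formula and week 52 simulations). If observed follow-up scores enter jointly, the estimate at 10-15% missing is about 0.74-0.77 at the pilot correlation and about 0.78-0.81 at an assumed 0.6. With arm included, 0.80 is recovered within simulation error.

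These figures assume 1:1 allocation, a constant effect over visits, and equal missingness in both arms, completely at random. The article's follow-up rates come from other studies by the same investigators; higher missingness here would enlarge the bias. It is worth correcting because the bias falls on the one analysis meant to separate the effect of missing data from everything else.

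**What to change.** Amend the predictor list in the Missing Data section:

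- Impute separately within each arm (a BY statement on group in Proc MI), or include arm as a variable in a single run. Imputing by arm also lets relations with other variables differ between arms, which suits the planned site-by-group test.
- Put leg pain at baseline and at weeks 3, 12, 26 and 52 in the same run, so that observed visits explicitly inform missing ones.
- Add the minimisation factors, which the analysis model adjusts for, and site.
- State that the imputation covers all randomised patients, including those without any follow-up score, whom the mixed model leaves out.

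The cost is a few lines of SAS and no new data. An analysis that shifts the imputed scores by a fixed amount, and a larger number of imputations, are optional additions and not needed to correct this fault.

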### Analysis of Biomechanical Measures

First, baseline measures of continuous spinal motion, postural sway, response to sudden load, and flexion-relaxation in the patients with BRLP will be compared to data (unpublished) from previous trials of patients with sub-acute and chronic low back pain *without *radicular pain. Next, we will explore effects of these measures after 12 weeks of active care, taking into account gender and body mass index. If there are unbalanced baseline or other confounding variables, we will also control for these in the analysis. Finally, we will examine and describe the bivariable relationships between our primary outcome, leg pain, and each biomechanical variable.

### Patient Interview Analyses

Content analysis using an inductive approach[104] will be used to identify categories and themes that occur in the transcribed text generated from the qualitative interviews[105].

The text of ten interviews will be read independently by two investigators from each site to gain an overall impression and to establish and define preliminary codes in response to the proposed questions[106,107]. After the initial analysis, the investigators will meet to reach a consensus on preliminary codes. These codes will be entered into a "code book," which will provide a detailed definition for each code[105]. Information related to methodological decisions and their rationale will also be documented[104]. Subsequent transcripts will be independently reviewed to identify and code text segments and to assess the inter-rater reliability of text coding. Kappa values of less than 0.8 will necessitate review of the coding structure.

Categorized information from the transcribed interviews will be entered in matrices to organize and display categories by treatment groups as a means of illustrating relationships among categories[108]. This information will then be summarized and interpreted.

